**Methods:**

The DTP is a complex educational intervention that consists of two workshops, a coaching program, access to an internet forum, and a Computerized Clinical Decision Support System on dementia diagnostics. One hundred duos of GPs and nurses will be recruited, from which 2/3 will be allocated to the intervention group and 1/3 to the control group. The effects of implementation of the DTP will be studied in a cluster-randomised controlled trial. Primary outcomes will be the number of cognitive assessments and dementia diagnoses in a period of 9 months following workshop participation. Secondary outcomes are measured on GP and nurse level: adherence to national guidelines for dementia, attitude, confidence and knowledge regarding dementia diagnosis and management; on patient level: number of emergency calls, visits and consultations and patient satisfaction; and on caregiver level: informal caregiver burden and satisfaction. Data will be collected from GPs' electronic medical records, self-registration forms and questionnaires. Statistical analysis will be performed using the MANOVA-method. Also, exploratory analyses will be performed, in order to gain insight into barriers and facilitators for implementation and the possible causal relations between the rate of success of the intervention components and the outcomes.

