## Methods

### Study design and setting

This study is an outcome assessor-blinded randomised controlled trial. A cluster-randomised design will be used to compare duos of GPs and nurses (Figure 1).

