### Bias control and randomisation

Randomisation will take place after measurement of baseline data. Duos of GPs and nurses will be randomly allocated to one of the two conditions: 1. Dementia Training Program (DTP) and 2. no training at all; control group. (Figure 1). Randomization will be concealed; a person who is not responsible for recruiting subjects and has no knowledge of the study conduct will perform it on a computer.

Cluster-randomisation will be performed in order to avoid contamination by the effects of possible exchange of information within a cluster. A cluster was defined as all GPs working in the same practice or as all GPs working together with the same nurse.

In order to assure an equal distribution of baseline characteristics, duos will be randomised with adaptive weights regarding cluster size (one vs. more than one GP), age, sex, high or low percentage of elderly patients in practice (< or > 15%), practice location (rural or urban area) and nurse affiliation (district or practice).

Adherence to guidelines will be assessed by two independent researchers. In order to exclude the possibility of detection bias, these researchers will be blinded to the outcome of randomization.

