### Outcome measures and data collection

Primary outcome measures are the numbers of cognitive assessments and dementia diagnoses over a period of nine months, which will be measured at baseline (T0) and nine months later, at the end of the study (T1). Secondary outcomes are GPs' and nurses' attitude, confidence and knowledge regarding dementia diagnosis and management, which will be measured at baseline (T0) and nine months later, at the end of the study (T1). Other secondary outcomes are the rate of adherence to national guidelines for dementia diagnosis and management, patient satisfaction, informal carer burden and satisfaction, number of emergency calls, visits and consultations. Baseline demographic characteristics collected from GPs and nurses are: age, sex, practice experience, practice size, percentage of elderly people > 65 years and the availability of chronic disease management programs in practice. Baseline demographic characteristics collected from patients and their informal caregivers are: age, sex and co-morbidity (Table 1).

**Table 1 T1:** Outcome measures

**Variable**	**Primary outcomes**	**Secondary outcomes**	**Background**	**Instrument/Source**	**T_0_**	**T_1_**	**T_x_**

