### Sample size calculations

We expected a change in the primary outcome measure of the incidence of dementia diagnoses and cognitive assessments from 50% to 65% of the total population of dementia. In previous studies on implementation of several other guidelines in general practice the average change was 10% [43]. However, these implementation studies focused on diseases, to which GPs already showed a high adherence to the guidelines. Because of the low adherence to dementia guidelines we saw more room for improvement and therefore we expected a change of 15% to be realistic. Cluster randomisation was taken into account when we calculated the sample size needed. In this calculation, the ratio between the number of duos in the control group and the number of duos in the intervention group was 1:2. Clusters are expected to include 5 patients on average. Intra class correlation (ICC) is expected to be 0.05 or lower. For a power of 0.80, and two-sided testing at 0.05, a total of 91 general practitioners is required.

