### Statistical analysis

In addition to a confirmatory analysis using the MANOVA-method, we will also perform an exploratory analysis. The aim of the exploratory analysis is to gain more insight into possible causal relations between the rate of success of the intervention components and the outcomes. Possible mediator variables are change in knowledge, attitudes and collaboration rate. We will design a path-model, specifying hypothesized relations between predictors, mediators, moderators, and effects, and we will test its goodness of fit with the data. In this way we hope to be able to specify the most plausible interdependence pattern between the variables used in the present study.

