Secondly, we cannot exclude the possibility of contamination arising by chance contacts and possible knowledge exchange between GPs and nurses from different allocation conditions. We try to overcome this problem by cluster randomization: GPs from the same practices and GPs working with the same nurses are allocated to the same group.

Finally, performance bias can occur. GPs and nurses are fully aware of their assignment to either the experimental or the control group. We try to overcome this problem by reminding participants in the control group every two months of their involvement in the study.

In spite of these elements of bias, the results of this trial may provide useful information for policy makers and developers of continuing medical education. The intervention is designed according to recently reported MRC guidelines and educational standards; exploratory analysis will reveal its successful elements. In the study design, bias is avoided if possible and still its setting is one of every day practice. Dissemination of the results of this study is planned for 2009.

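### The only confirmatory method named is MANOVA, with no provision for the randomised practice or nurse group; if run per GP or duo, its type I error exceeds 5% wherever clusters hold several positively correlated GPs

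*Protocol article*

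**What the plan says.** **Unit randomised.** Bias control and randomisation defines it: "A cluster was defined as all GPs working in the same practice or as all GPs working together with the same nurse". The Discussion confirms that such GPs stay together: "GPs from the same practices and GPs working with the same nurses are allocated to the same group". Clusters with several GPs are foreseen, because one of the balancing factors is "cluster size (one vs. more than one GP").

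**Unit compared and measured.** Study design and setting states: "A cluster-randomised design will be used to compare duos of GPs and nurses (Figure 1"). The primary outcomes are counts: "Primary outcome measures are the numbers of cognitive assessments and dementia diagnoses over a period of nine months". Table 1 lists both counts under the heading for GPs and nurses.

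**Analysis.** The abstract says: "Statistical analysis will be performed using the MANOVA-method". The Statistical analysis section says: "In addition to a confirmatory analysis using the MANOVA-method, we will also perform an exploratory analysis". Neither place mentions a cluster term, a random effect, a robust variance or a summary per cluster.

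**Sample size.** Here clustering does appear: "Cluster randomisation was taken into account when we calculated the sample size needed". The inputs are 5 patients per cluster, an ICC of 0.05 or lower and a total of 91 GPs.

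**The concern.** Standard MANOVA takes its rows as independent. GPs in one practice, or sharing one nurse, receive the same allocation and work in the same setting, so their counts are likely to be positively correlated. If each GP or duo is a row, the between-arm comparison is credited with more independent information than the randomisation supplies. P-values are then too small and intervals too narrow, and the test that carries the main conclusion does not hold its two-sided 0.05 level.

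The sample size calculation does not settle this. Its cluster is 5 patients and its total is counted in GPs, so it allows for patients within a GP and not for GPs within a randomised practice or nurse group.

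**Working it through.** **1. The plan's own figure.** Inputs from Sample size calculations: 50% vs 65%, ratio 1:2, power 0.80, two-sided 0.05, 5 patients per cluster, ICC 0.05.

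- Pooled proportion: (0.50 + 2 × 0.65)/3 = 0.60.
- Control patients: [1.96 √(0.60 × 0.40 × 1.5) + 0.8416 √(0.25 + 0.2275/2)]² / 0.15² = 126. With 252 in the intervention arm, the total is 378.
- Design effect: 1 + (5 − 1) × 0.05 = 1.20. Then 378 × 1.20 / 5 = 90.7, so 91 GPs, as stated.
- Without the design effect: 378/5 = 75.6, so 76 GPs.

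The 91 is correct on its own inputs. It also shows that the calculation treats one GP's 5 patients as the cluster.

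**2. Correlation between two GPs in one randomised cluster.** The document does not give this, so it is an assumption. Let a share f of the 0.05 lie at practice or nurse level and the rest at GP level, with each GP summarised over 5 patients:

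r = 0.05f / (0.05 + 0.95/5) = 0.05f / 0.24

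- f = 1: r = 0.208
- f = 1/2: r = 0.104
- f = 1/5: r = 0.042

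**3. Type I error of a two-outcome MANOVA with one row per GP.** With g GPs per cluster the design effect is DE = 1 + (g − 1)r. Taking the same r for both outcomes, the large-sample error of a nominal 5% test on 2 degrees of freedom is exp(−5.991 / (2 DE)).

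| Share f | g = 1 | g = 2: DE, error | g = 3: DE, error |
|---|---|---|---|
| 1 | 5% | 1.208, 8.4% | 1.417, 12.1% |
| 1/2 | 5% | 1.104, 6.6% | 1.208, 8.4% |
| 1/5 | 5% | 1.042, 5.6% | 1.083, 6.3% |

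If 0.05 is instead taken directly as the between-GP correlation, DE is 1.05 and 1.10, giving 5.8% and 6.6%, inside the same ranges.

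**4. Interval width.** The ratio of the unadjusted to the correct width is 1/√DE: 0.98 to 0.91 for two GPs (DE 1.042 to 1.208) and 0.96 to 0.84 for three (DE 1.083 to 1.417).

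**5. Simulation check.** Two separate simulations of the two-outcome test (91 GPs, 2:1 by cluster, r = 0.208, outcome correlation 0.7, 4000 runs each) gave 8.3% and 9.2% for pairs, and 11.6% and 11.8% for triples. The same test on one mean per cluster gave 4.4% to 5.8%. So MANOVA itself is not the problem; the row is.

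**6. Patient and carer outcomes.** If these are analysed per person, 5 patients per GP give DE = 1.20 even with one GP per cluster. For a single outcome the error is 2[1 − Φ(1.96/√1.20)] = 7.4%.

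**The case against.** **The row is not stated.** The article does not say what enters the MANOVA. One row per cluster, or cluster nested within arm, would be valid and still deserve the name. A condensed article may leave model terms to the full protocol or analysis plan. This stands, and it makes the point conditional. It does not dispose of the point: the article names a confirmatory method twice, says that duos are compared, and nowhere ties the method to the randomised cluster.

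**The sample size ICC does not contradict a GP-level MANOVA.** A reader might infer that the plan allows for clustering in the design and then discards it in the analysis. That goes too far. One count per GP already absorbs the correlation among that GP's patients, which is what the factor 1.20 covers. What remains unaddressed is GPs within a practice or nurse group.

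**The size may be slight.** The top of each range puts the whole 0.05 at practice or nurse level, while the plan calls it 0.05 or lower and applies it to patients within a GP. The share of single-GP clusters is unknown, and for those the counts show no inflation. This also stands, and it is why only a range is given.

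**Stronger readings.** A reader might suppose that a shared nurse raises the correlation to, say, 0.4, which would take the error to 12% to 20%, or that a shared nurse's questionnaire score is entered once for each GP. The document gives no such correlation and does not say how nurse scores enter, so neither is claimed.

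**Conclusion.** The point holds in conditional form. The named confirmatory method makes no provision for the unit randomised. If it is run with one row per GP or duo, as the design and outcome sections suggest, its error is above 5% whenever clusters hold several positively correlated GPs.

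The direction is clear and the size is not. It is nil with single-GP clusters, about 5.6% to 8.4% with two GPs per cluster, and about 6% to 12% with three. These figures assume a patient ICC of 0.05, 5 patients per GP, equal cluster sizes and a share of one fifth to all of the ICC at practice or nurse level. Per-person analysis of patient or carer outcomes would run at about 7.4% even with one GP per cluster.

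The document does not support saying that the trial's p-values will certainly be too small, since the unit of analysis is not spelled out. The figure of 91 GPs is not in error on its own inputs.

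**What to change.** In the abstract and the Statistical analysis section, state that the confirmatory analysis is done at the level of the randomised cluster. Either of these would do:

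- a MANOVA, or a simple comparison between arms, on one summary per cluster, such as the mean count per GP;
- a mixed or GEE model for each primary count, with the randomised cluster as grouping unit and a small-sample correction.

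Use the same cluster term for the questionnaire, patient and carer outcomes.

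The first option keeps the planned method and changes only its unit. The cost is a sentence or two of text and slightly wider intervals. Cluster membership is already known from the randomisation, so no new data are needed.

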## Abstract

**Background:**

Early diagnosis of dementia benefits both patient and caregiver. Nevertheless, dementia in primary care is currently under-diagnosed. Some educational interventions developed to improve dementia diagnosis and management were successful in increasing the number of dementia diagnoses and in changing attitudes and knowledge of health care staff. However, none of these interventions focussed on collaboration between GPs and nurses in dementia care. We developed an EASYcare-based Dementia Training Program (DTP) aimed at stimulating collaboration in dementia primary care. We expect this program to increase the number of cognitive assessments and dementia diagnoses and to improve attitudes and knowledge of GPs and nurses.

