**Informal carers**							
Age	□	□		Own questionnaire		□	□
Sex	□	□		Own questionnaire		□	□
Satisfaction intervention	□		□	Own questionnaire	□	□	
Burden informal caregiver	□		□	SSCQ^3^	□	□	

T_0 _is baseline measurement

T_1 _is follow up measurement, after 9 months

T_x _is 3 months after starting each assessment

^1 ^measurement of 'number' during a period of 9 months

^2 ^Electronic Medical Dossier

^3 ^Short Sense of Competence Questionnaire

Data on adherence to national guidelines, the number of emergency situations and the number of cognitive assessments and dementia diagnoses will be retrieved from GPs' Electronic Medical Records (EMD), from interviews with GPs and nurses and from self registration forms [41]. Self-made questionnaires will provide information on baseline characteristics, on data on GPs' and nurses' attitudes, competencies and knowledge regarding dementia diagnosis and management and on patient and informal carer satisfaction. Burden of informal carers will be assessed using the Short Sense of Competence Questionnaire (SSCQ) [42]. Data on duos' performance during the 'coaching phase' will be included in the analysis.

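### Knowledge and attitude change is measured only when the nine-month counts are complete, so the path model cannot separate mediation from reverse causation, and the article claims more for it than the design supports

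*Protocol article*

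**What the plan says.** **Mediators.** The Statistical analysis section adds an exploratory path model to the confirmatory MANOVA: "Possible mediator variables are change in knowledge, attitudes and collaboration rate". Goodness of fit is the only check named.

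**Timing.** Outcome measures and data collection states: "Secondary outcomes are GPs' and nurses' attitude, confidence and knowledge regarding dementia diagnosis and management, which will be measured at baseline (T0) and nine months". The second of these occasions, T1, closes the study. Table 1's footnote defines T1 likewise: "is follow up measurement, after 9 months". The only other time point, Tx, "is 3 months after starting each assessment", is tied to individual patients. The Abstract gives the count window: "Primary outcomes will be the number of cognitive assessments and dementia diagnoses in a period of 9 months following workshop participation".

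**Collaboration.** The Abstract presents it as the programme's purpose: "We developed an EASYcare-based Dementia Training Program (DTP) aimed at stimulating collaboration in dementia primary care". Neither the outcome text, nor Table 1, nor the data-source paragraph names a collaboration variable, instrument or time point.

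**Claims.** The Abstract and the closing paragraph of the Discussion both say that "exploratory analysis will reveal its successful elements". The first paragraph of the Discussion lists among the study's strengths that the analysis can show how components act and by which pathways.

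**The concern.** A mediator should come before the outcome it is meant to explain. Here the change score is observed only when the count is final. The protocol also describes a route in the opposite direction: coaching is triggered by each assessed patient, so a duo that assesses more patients may learn more. A positive association between knowledge change and count is then expected even if knowledge has no effect on the count.

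At stake is the second message of the trial, namely which parts of the programme work and why. The article names policy makers and developers of medical education as its audience. They could be told that the programme works by changing knowledge or attitude, or that a given component is responsible, on evidence that cannot show either.

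**Working it through.** **1. Order of measurement.** The counts run over the nine months after the workshops (Abstract, Methods; Table 1, footnote 1). Knowledge and attitude change is T1 minus T0, with T1 at month 9 (Outcome measures). The change is therefore known only when the count window closes. Table 1's tick marks are not legible in the copy reviewed, but the prose is clear.

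**2. The reverse route is in the design.** Under Phase 1, nurses discuss the first patient with a coach before and after the assessment, and the second afterwards. Nurses and GPs review each of the first three patients at six weeks and three months. Phase 2 presumes that the workshops and these reviews have trained them sufficiently. Doing assessments is thus an intended source of learning.

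**3. Why fit cannot settle direction.** Take allocation T, mediator M and count Y. The model T→M, T→Y, M→Y has three paths for three covariances. So has T→M, T→Y, Y→M. Both are saturated, both fit perfectly, and they imply opposite conclusions.

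**4. Size under zero mediation.** No correlation is given in the article, so every value here is an assumption. Let Y = aT + e and M = bY + cT + u, with no effect of M on Y.

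- Effect of T on M: ab + c.
- Slope of Y on M given T: b·var(e) / (b²·var(e) + var(u)).
- Spurious indirect effect: the product of the two.

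If c = 0, the share of the total effect a wrongly attributed to M is b²·var(e) / (b²·var(e) + var(u)) = r², where r is the within-arm correlation of Y and M. That is 9%, 25% and 49% at r = 0.3, 0.5 and 0.7.

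The workshops also teach directly, so c > 0 is more realistic. With unit variances and a = c = 0.5 SD, the spurious indirect effect is (0.5b + 0.5)·b / (b² + 1). At b = 0.3 this is 0.65 × 0.3 / 1.09 = 0.179 SD, or 0.179 / 0.5 = 36% of the total effect.

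A simulation of 67 and 33 duos (two thirds and one third of 100), 4,000 runs per setting and duos treated as independent, agrees:

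| b (assumed) | M→Y path significant, c = 0 | M→Y path significant, c = 0.5 | Spurious indirect effect, c = 0.5 (SD) |
|---|---|---|---|
| 0 | 5.1% | 6.0% | 0.001 |
| 0.1 | 16.2% | 16.1% | 0.054 |
| 0.2 | 50.4% | 49.5% | 0.115 |
| 0.3 | 83.2% | 82.6% | 0.179 |
| 0.5 | 99.7% | 99.8% | 0.298 |

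These rates concern the mediator-to-count path alone, not a joint test of the indirect effect.

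**5. Components.** Bias control and randomisation gives two conditions, the whole programme or no training. Any comparison by component uptake is made among trained duos and is not randomised.

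**6. Collaboration.** The nearest sources are coach diaries, which record the coaches' own work, and performance data from the coaching phase. Control duos are not coached during the trial, so neither source covers them.

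**7. The plan's own figure.** The 91 GPs are not in dispute and reproduce: 378 patients × 1.2 (design effect 1 + 4 × 0.05) / 5 = 90.7.

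**The case against.** The operative section is cautious. It calls the analysis exploratory, speaks of possible relations and possible mediators, and fixes no path diagram. The outcomes in the model could include guideline adherence, carer burden or satisfaction, so the arrow from month-9 change to count is not formally specified. The article also does not say that randomisation isolates components; variation in uptake can be studied observationally.

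Most of this stands, and it limits the point. It does not rescue the statements in the Abstract and Discussion, which carry no such caution. The counts are the primary outcomes, so they are the natural targets of a mediation analysis.

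Three stronger readings are tempting and not supported:

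- *A reader might infer that collaboration is not measured at all.* The article only states no measure. It mentions interviews, self-registration forms and self-made questionnaires, and a fuller protocol may define one. Taken alone, the missing definition would be a detail that a condensed article may leave out.
- *A reader might take the r² shares as this trial's bias.* They rest on an assumed r and on a model in which training does not itself raise knowledge. They show that the problem can be large, not how large it is here.
- *A reader might infer that the trial's main result is undermined.* The comparison of counts by allocation does not use the mediators.

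**Conclusion.** The point holds for the exploratory path analysis and for the claims built on it. With change measured only from T0 to T1, a model that treats it as a mediator of the counts cannot distinguish mediation from learning through assessments. The design gives no randomised evidence on components, and collaboration has no stated measure. The promises to reveal successful elements and to show pathways therefore exceed what the trial can deliver.

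No size can be fixed from the article. Under the assumptions shown, the false share ranges from negligible when counts barely affect knowledge to more than half of the total effect (0.298 / 0.5 = 60%) at b = 0.5 with a direct training effect. The judgement that reverse causation is plausible rests on the protocol's own coaching scheme, not on these figures. This should be corrected, but it does not threaten the confirmatory result.

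**What to change.** 1. **Wording, at no cost.** In the Abstract and in the first and last paragraphs of the Discussion, describe component and pathway results as non-randomised associations that generate hypotheses.
2. **Month-9 change.** Do not use it as a mediator of the counts. It remains a valid secondary outcome.
3. **Preferably, one early repeat of the existing questionnaire.** Give it soon after the second workshop, at a matching date in control duos, and relate it only to counts accruing afterwards. The cost is one more questionnaire for about 100 duos and one more exposure of controls to its content. This addresses mediation by workshop learning only and would miss learning through later coaching. The mediator is still not randomised, so the result stays exploratory.
4. **Collaboration.** Keep it as a mediator only if it is measured in both arms, is defined for duos with no assessments and is obtained before the counts it is to explain. A share of assessed patients with input from both professionals would fail the last two conditions. Otherwise drop it from the model.

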## Discussion

In this paper we described the study design of a randomized controlled trial that evaluates the effects of a Dementia Training Program (DTP) for duos of GPs and primary care nurses. A novelty in this program is the training in fixed collaborative duos. We chose focus on collaboration, because dementia care management in collaborative interdisciplinary teams was found to be effective in improving the quality of care [31]. Another novelty in our approach is the inclusion of an individual coaching program in the DTP. This educational method appears to be highly effective modifying professional behaviour [32]. Whereas some studies used single interventions [27], we developed multifaceted intervention, since multifaceted interventions are usually more effective [33]. For the design and evaluation of the DTP, we used the MRC framework [44]. The exact content of the DTP will be described in more detail in a separate article. Methodologically strong elements in this study are the following. We avoid selection bias by computerized randomization and minimisation. Two independent blinded outcome assessors will contribute to overcoming detection bias. In addition to a confirmatory analysis, we will perform an exploratory analysis. In this way, we can clarify how certain intervention components influence the rate of success and through which pathways.

Below, we describe the design characteristics that may interfere with the reliability and validity of the future results. Firstly, the method of participant recruitment may threat the external validity of the study: GPs and nurses are free to decide whether they want to participate. This may mean that this group of participants is more interested in dementia care than their average colleagues. Therefore, they may be more motivated to learn and perform better than their non-participating colleagues would do after receiving the same training. In addition, they may already be taking better care of dementia patients and their caregivers than their non-participating colleagues. However, the possible effects of this bias would run counter to our hypotheses by negatively affecting the chances to detect differences between the experimental and the control group. These effects might affect the probability of making a type II error (incorrectly accepting H-0) but they cannot cause the making of a type I error (incorrectly rejecting H-0).

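### Goodness of fit is the only criterion named for the path model, but overall fit cannot tell real mediation from absent mediation, so it cannot carry the promised statements about pathways and successful elements

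*Protocol article*

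**What the plan says.** The Statistical analysis section of the protocol article sets an exploratory analysis beside the confirmatory MANOVA. Its purpose is modestly put: "The aim of the exploratory analysis is to gain more insight into possible causal relations". Three candidate mediators are listed: "Possible mediator variables are change in knowledge, attitudes and collaboration rate". A path model linking predictors to effects through mediators, with moderators, is to be drawn up in advance. The authors will then "test its goodness of fit with the data. In this way we hope to be able to specify the most plausible interdependence pattern" among the study's variables. No other criterion and no rival model is named.

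The Discussion is firmer. Among the strengths of the study it says "In this way, we can clarify how certain intervention components influence the rate of success and through which pathways", and its closing paragraph says "exploratory analysis will reveal its successful elements". The Discussion part of the abstract makes the same promise.

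**The concern.** A goodness-of-fit test takes the proposed model as its null hypothesis and examines only the restrictions the model imposes, that is, the paths omitted from it. It does not ask whether the drawn paths (programme to knowledge, attitude or collaboration, and from there to the outcome) differ from zero. A mediation model with free paths contains the case in which all of them are zero. If the programme changes nothing, that model is still correctly specified and should pass. If every possible path is drawn, no degrees of freedom remain and the model fits any data perfectly.

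Calling a pattern the most plausible one is also a comparison, and the text supplies nothing to compare it with. At stake is the mechanism message: which elements of the training work, and by what route. Developers of further education could act on that message, and good fit alone would not support it.

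**Working it through.** **The plan's own figure.** The article gives no number for the path model, so the only figure to reproduce is the sample size (Sample size calculations): 50% against 65%, control to intervention 1:2, power 0.80, two-sided 0.05, 5 patients per cluster, ICC 0.05.

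- Control patients: n = [z(0.975)·√((1 + 1/2)·0.60·0.40) + z(0.80)·√(0.50·0.50 + 0.65·0.35/2)]² / 0.15² = (1.176 + 0.508)² / 0.0225, which gives 126.
- Total: 126 + 252 = 378.
- Design effect: 1 + (5 − 1)·0.05 = 1.2, so 378 × 1.2 = 453.6 patients.
- Clusters: 453.6 / 5 = 90.7, rounded up to 91.

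The stated 91 reproduces. With the planned recruitment of 100 duos (Study population), it gives the range N = 91 to 100 used below.

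**Inputs for the fit test.** From the document: N = 91 and 100, 2:1 allocation, three mediators. Assumed, because the article does not give them: an exact-fit likelihood-ratio test at 5%, one continuous outcome, residual SD of 1 throughout, independent duos, and the effect sizes shown. There were 20,000 simulated trials per scenario.

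**Formula.** The model is programme to three mediators to outcome, with no direct path and mediator residual covariances free. Five variables have 10 pairwise covariances. The model uses 3 (programme-mediator) + 3 (mediator-outcome) + 3 (mediator-mediator) = 9, leaving 1 degree of freedom. The statistic is LR = N·ln(RSS₀/RSS₁), where RSS₀ regresses the outcome on the mediators and RSS₁ adds the programme. The model passes if LR is below the 95th percentile of chi-square on 1 df.

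| Truth (assumed) | Passes, N = 91 | Passes, N = 100 |
|---|---|---|
| All paths zero, mediators uncorrelated | 94.2% | 94.4% |
| All paths zero, mediator residuals correlated 0.3 | 94.6% | 94.7% |
| Real full mediation (programme to mediator 0.5, mediator to outcome 0.3) | 94.2% | 94.0% |
| Direct effect only, 0.3 SD | 71.8% | 70.0% |
| Direct effect only, 0.5 SD | 39.1% | 34.7% |

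A version with two mediators and 6,000 trials per scenario agrees:

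- No effect anywhere: 94.3% (N = 91) and 94.8% (N = 100).
- Training raises the mediators by 0.5 SD but nothing reaches the outcome: 94.9% and 95.0%.
- Real mediation: 93.8% and 94.4%.
- Direct effect only: 72.9% and 70.4% at 0.3 SD; 38.9% and 34.4% at 0.5 SD.

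**Contrast with testing the paths.** On the three-mediator data, take a pathway as present when both its programme-to-mediator and mediator-to-outcome coefficients are significant at 5%. At least one pathway is then flagged in 0.7% to 0.8% of trials when all paths are zero, and in 85% (N = 91) to 89% (N = 100) when mediation is real. The data can address the question, but overall fit does not.

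**Sensitivity to the diagram.** Fixing the mediator residual covariances at zero gives 1 + 3 = 4 degrees of freedom. With truly uncorrelated mediators, that model passes in 93.8% to 93.9% of trials when all paths are zero and in 94.0% to 94.1% under real mediation. With residuals correlated at 0.3 and all paths zero, it passes in only 2% to 3%. That rejection reflects the correlation and says nothing about mediation.

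**The case against.** The strongest reply is that the article states no acceptance rule: no fit statistic, no level, no diagram. It does not say that path coefficients will be ignored, and fitting a path model produces them. Checking fit is a normal step, and indirect-effect intervals or a list of rival models are details a fuller plan may hold. The planned model also has moderators and component-level predictors, so it may carry more restrictions than the one simulated. Finally, the Statistical analysis section is cautious in tone and keeps this analysis apart from the confirmatory one.

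Much of this stands. The absence of bootstrap or interval details is not the point and would not be a finding. A reader might infer that the 95% figure is a property of the plan; it is not, since it depends on the assumed test and on mediator covariances being free or truly zero. A reader might also infer that only one model will ever be fitted, which the text does not say.

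What does not fall away is the inference as written. Fit is the one criterion named, the next sentence draws the pattern of relations from it, and the Discussion turns this into unhedged statements about pathways and successful elements. A larger model does not repair that: more omitted paths give the test more restrictions to check, but drawn paths remain untested by overall fit.

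**Conclusion.** The point holds as an inference that does not follow. Overall fit cannot separate real from absent mediation: under an exact-fit test at 5% with mediator covariances free, the pass rate is about 94-95% in both cases at N = 91 to 100. The equality is structural. The exact percentages rest on the assumed test, level and model.

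Two stronger readings are not supported. One is that good fit is to be expected whatever the truth. Against an omitted direct path the test has some power: the wrong full-mediation model passes in about 34-39% of trials at 0.5 SD, so it is rejected in most of them, though it still passes in 70-73% at 0.3 SD. The other is that the trial's main result is compromised. The confirmatory analysis does not use the path model and is unaffected. Because the analysis is labelled exploratory, severity is minor to moderate.

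**What to change.** - State that overall fit is a check on the model and not evidence for a pathway.
- Base pathway statements on estimated indirect and direct effects with 95% confidence intervals that respect the clusters (for example, a bootstrap that resamples clusters). Claim an indirect pathway only if the interval for its indirect effect excludes zero.
- Before outcomes are seen by arm, name the rivals: at least a direct-effect-only model without mediation, and mediation plus a direct effect. Compare nested models by likelihood ratio and non-nested ones by BIC. Mediation plus direct effect with free covariances has no degrees of freedom, so it serves as a comparator and cannot itself be tested for fit.
- Reword the Discussion and abstract so that the analysis generates hypotheses about pathways and successful elements. This is needed even with the better method, because the arms differ by the whole programme and neither the components nor the mediators are randomised separately.

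The cost is a few sentences, a few extra model fits on data already being collected, and a more modest claim about mechanism.
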